### Timing of interim analyses

Interim analyses need sufficient numbers of patients at EOT + 12 to give a reasonable probability of stopping a genuinely inferior group. Therefore, it was decided to perform analyses after the first month such that at least one inferior group has a 0.3, 0.5 or 0.7 average probability of being stopped were this to be the first interim analysis, assuming that cure rates are uniformly distributed on (0.6, 0.9) and given projected recruitment (Supplementary Table 2, Additional file 1). An average probability is used to reflect the uncertainty about the true cure rates; for low cure rates, the probability of stopping a group can be substantially higher (Fig. 2). An additional analysis before these thresholds will allow for any groups with a very low cure rate below the anticipated minimum of 60% to be detected early despite the very small probability of detecting a group with a cure rate between 60% and 90%.

**Fig. 2 Fig2:**
[figure not shown]
Initial probability of stopping groups over an estimated recruitment schedule for various true cure rates. The average true cure rate is uniformly distributed over 60–90%. Probabilities are calculated assuming no previous interim analysis. The total numbers of patients recruited at each month, of a total target of 1092, are 113 at 5 months, 153 at 6, 205 at 7, 257 at 8, 309 at 9, 361 at 10, 413 at 11, 465 at 12, 517 at 13, 569 at 14, 621 at 15, 673 at 16, 725 at 17, 777 at 18, 829 at 19, 881 at 20, 933 at 21, 985 at 22, 1037 at 23 and 1092 at 24. See Supplementary Figure 1, Additional file 1 for the cumulative probability of stopping a group.

Four analysis time points were chosen to provide multiple opportunities to detect failing groups while allowing adequate time between analyses for the accrual of patients and outcome data and preventing an unnecessary burden on time and resources needed for analyses and subsequent DMC meetings. The highest probability threshold (0.7) is determined by the maximum average cure rate of the genuinely inferior groups and by the recruitment schedule, as analyses need to be performed sufficiently early enough to gain the benefit of randomly assigning remaining patients to the other groups. The other thresholds (0.3, 0.5) were evenly spaced across the probabilities of stopping a group with an average cure rate, taking into consideration the first, early DMC meeting not based on these probabilities.

Therefore, considering the underlying projected recruitment, we expect the interim analyses to take place after 7, 10, 13 and 18 months. The number of patients in each group and the probability of stopping an inferior group of each strategy type at these analyses are listed in Table 4. By assessing the cumulative probability of stopping a group (Supplementary Fig. 1, Additional file 1), our schedule provides a balance between having more frequent meetings, which have a lower probability of stopping groups at any individual meeting but allow for earlier detection of poorly performing groups, and less frequent meetings, which have a higher probability of stopping a group but its low performance is detected later. The exception to this is having analyses every month but this schedule is impractical because of the resources required for an interim analysis.

**Table 4 Tab4:** Timing of interim analyses

	First	Second	Third	Fourth
Months since recruitment started	7	10	13	18
Total recruited	205	361	517	777
Total at EOT + 12 weeks	44	144	286	533
At EOT + 12 weeks in each:				
PEG-IFN group	5	14	24	42
RGT group	3	11	21	39
Induction/maintenance group	2	8	17	35
Average probability genuinely inferior group will be stopped^a^				
PEG-IFN groups	0.124	0.297	0.537	0.710
RGT groups	0.021	0.313	0.440	0.665
Induction/maintenance groups	0.070	0.150	0.431	0.593

*Abbreviations*: *EOT + 12* 12 weeks after the end of treatment, *PEG-IFN* pegylated-interferon, *RGT* response-guided therapy

^a^ Assuming true cure rate uniformly distributed over 60–90%

As this is only projected recruitment, sensitivity analyses were performed to examine the effect of faster or slower recruitment (Supplementary Table 3, Additional file 1). These indicate that changes to the recruitment schedule alter only the timing of the analyses; the number of patients in each analysis differs by less than the estimated number recruited in 1 month. Therefore, if there are significant delays in recruitment, interim analyses will be timed such that they include a similar number of patients at EOT + 12 to that in the expected schedule. Sensitivity analyses also explored changing the lower bound of the distribution over which cure rates of genuinely inferior groups are assumed to be distributed to below 60% (Supplementary Table 4, Additional file 1) but this had minimal effect on the timing of initial interim analyses. There were greater differences in the timings of the last analyses, but the timing of this analysis is the most flexible and can be determined on the basis of observed rather than assumed true cure rates.

### Power for final analysis

Given the lack of knowledge of the standard 12-week cure rates for this population (anticipated 50% of patients with genotype 6) and how cure rates in the shortened treatment with ribavirin groups will compare to these and to shortened treatment without ribavirin, there is uncertainty regarding the overall power for the final analysis even if the overall cure rate is 95% (Table 5). If we assume equality between regimens and a 5% absolute difference for ribavirin, then these constraints mean that the cure rates in each group are completely determined by the difference between the shortening strategies. Non-inferiority can exist between the standard duration group and the pooled shortening strategy groups, the shortening strategy without ribavirin groups, or the shortening strategy with ribavirin groups, meaning that the shortening strategy with ribavirin groups can have cure rates 2.5% higher than, 5% higher than or equal to the standard duration groups respectively. These alternatives are shown in different columns of Table 5.

**Table 5 Tab5:** Group-specific cure rates and power for 1092 patients with an overall 95% cure rate

	Ribavirin group cure rate compared with 12 week standard treatment cure rate		
	5% higher	2.5% higher	Equal
Group-specific cure rates:			
Standard 12-week treatment groups	93.3%	95%	96.7%
Shortened treatment with ribavirin groups	98.3%	97.5%	96.7%
Shortened treatment without ribavirin groups	93.3%	92.5%	91.7%
Power for a:			
5% non-inferiority margin for regimen comparison	99%	98%	97%
10% non-inferiority margin for strategy comparison	100%	100%	96%
5% absolute difference for ribavirin comparison	98%	95%	91%

Group-specific cure rates are such that overall cure rate in 1092 patients is 95%, ribavirin effect between shortened treatment groups is 5% and there is no effect of regimen. The effect of ribavirin in shortened treatment compared with standard treatment is varied to reflect uncertainties in the cure rates and to vary the no effect of strategy between standard treatment and shortened treatment without ribavirin, shortened treatment with ribavirin and pooled shortened treatment groups. Power is calculated with one-sided alpha of 0.05 for non-inferiority margins and two-sided alpha of 0.05 for superiority comparisons reflecting the design. Power assumes that no groups have been stopped during recruitment.

Power to determine non-inferiority for the regimen comparison using a 5% margin is mostly unaffected by assumptions about different values for the standard 12-week cure rate and effect of ribavirin, and power remains close to 100%. Power to determine non-inferiority in the strategy comparison using a 10% margin is similarly unaffected, and power remains close to 100% when comparing the pooled shortening strategy groups against standard duration. For superiority comparisons, power to detect a 5% absolute difference in the ribavirin or regimen comparison remains high at more than 90% regardless of the standard duration cure rate and ribavirin effect.

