## Methods

### Trial design

VIETNARMS is a parallel-group open-label factorial trial (ISRCTN61522291); 1092 patients will be factorially randomly assigned 1:1 to two different WHO-recommended dual DAA regimens (sofosbuvir/velpatasvir versus sofosbuvir/daclatasvir), 1:2:2:2 to the standard licensed 12-week treatment versus 4-week treatment with PEG-IFN + DAA versus 4- to 12-week response-guided therapy (RGT) versus 12-week treatment using an induction/maintenance approach, and (if not randomly assigned to standard 12-week treatment) 1:1 to adjunctive ribavirin versus no ribavirin for the duration of their DAA treatment (Fig. 1). Randomisation will be stratified by genotype 6 versus all other genotypes. Patients randomly assigned to the PEG-IFN strategy will receive DAAs for 4 weeks with weekly PEG-IFN for 4 weeks starting at day 7. Treatment length for those randomly assigned to RGT will be determined by HCV viral load (VL) at day 7 and based on predicted viral kinetics [27]: those with VL of less than the lower limit of quantification (LLOQ) will receive 4 weeks of treatment, those with VL LLOQ-250 IU/mL will receive 8 weeks and all others will receive 12 weeks. Patients randomly assigned to induction/maintenance will receive 12 weeks of treatment: 2 weeks of daily treatment (induction phase) followed by 10 weeks of 5-day treatment per week, taking weekends off from the first weekend following their full 2-week treatment. Each strategy reduces DAA exposure and has other benefits, such as compatibility with directly observed therapy programmes (as used for tuberculosis) but with other additional costs (Table 1). Within the trial, any patient not achieving cure with their first-line treatment will receive 12 weeks of retreatment with the alternate drug regimen to the one they were originally randomly assigned plus ribavirin.

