### Sample size

The sample size of the trial was derived on the basis of the null hypothesis that the true cure rate was 90% in each group compared with an alternative, unacceptably low, cure rate of 70%; assessment of power at the final analysis given this sample size is discussed later. For a single stratum within a single randomly assigned group, given 90% power and one-sided alpha of 0.05, and 5% loss to follow-up by EOT + 12, 39 patients would be required per group to exclude the cure rate being lower than 70% based on a single-group test. There are 14 groups and two genotype strata, giving a total sample size of 1092 patients (39*14*2). For final comparisons at trial closure, the null hypothesis is that all groups will achieve the more than 90% cure target and be included in the final analysis. There will then be 546 per group for the regimen comparison (non-inferiority; comparing the two WHO-recommended drug regimens against each other), 156 in the control group and 312 per intervention group for the strategy comparison (non-inferiority; comparing each of the three treatment-shortening strategies versus the licensed 12-week control duration), and 468 per group for the ribavirin comparison (superiority; comparing each treatment-shortening strategy with and without ribavirin). The total sample size is fixed at 1092 patients; if individual groups are stopped early, any subsequent patients will be randomly assigned to open groups where possible (depending on the delay between randomisation, identification of primary endpoints and interim analyses), so numbers in each fully recruited group may be higher. This is appropriate in a pragmatic trial, where the goal is to maximise information gained about many different strategic approaches to treatment rather than to minimise sample size per se.

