The choice of the non-inferiority margin was based on clinical judgement and the size of margins used in other trials of anti-infectives with relatively low failure rates such as community-acquired pneumonia [30]. In particular, a smaller 5% margin is chosen for the drug comparisons because in practice they are likely to have similar advantages and disadvantages. In contrast, the different drug-sparing strategies have a variety of different advantages and disadvantages (in terms of additional visits vs. less drug vs. different drugs vs. weekends off; Table 1) which could be differentially balanced against overall cure rates, particularly considering impact on health-care provision (e.g., through directly supervised therapy). Thus, a greater non-inferiority margin (here 10%) is relevant to drug-shortening because the potential benefit in terms of numbers treated for the same fixed budget is much greater. Regulatory guidance recommends that non-inferiority margins be chosen to ensure that the difference between an intervention and the active control (here 12 weeks’ duration) would not exceed that between the active control group and a hypothetical placebo (or other standard control group, here the previous standard of care of 12–48 weeks of PEG-IFN) [30]. As cure rates with 12–48 weeks of PEG-IFN were about 70% in genotype 6 [31], with similar or lower cure rates in other genotypes, and as we expect more than 90% SVR12 in all groups, our non-inferiority margins of both 5% for the regimen comparison and 10% for the strategy comparison would ensure this.

From initial power calculations based on all 14 randomly assigned groups, assuming that the overall cure rate is 95%, the fixed total sample size of 1092 patients above provides 97% power to demonstrate non-inferiority between drug regimens based on a 5% margin and 96% power to demonstrate non-inferiority between shortening strategies based on a 10% margin, both with one-sided alpha of 0.05. For superiority comparisons (conducted for ribavirin and any comparison that meets non-inferiority above) and two-sided alpha of 0.05, these numbers provide more than 90% power to detect absolute differences in SVR12 of 5% for regimen or ribavirin comparisons and more than 80% power to detect absolute differences in SVR12 of 7% or more for the strategy comparisons.

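### Table 5's outer columns do not average to the stated 95% overall cure rate under the trial's own allocation, so their power figures belong to overall rates of about 95.5% and 94.5%

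*Protocol article*

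**What the plan says.** Table 5 and its note hold the overall cure rate fixed: "Group-specific cure rates are such that overall cure rate in 1092 patients is 95"%, with a 5-point ribavirin effect among shortened groups and no regimen effect. The three columns vary only how the ribavirin groups compare with standard 12-week treatment.

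| Column | Standard | Shortened + ribavirin | Shortened, no ribavirin | Power: regimen / strategy / ribavirin |
|---|---|---|---|---|
| *5% higher* | 93.3% | 98.3% | 93.3% | 99 / 100 / 98% |
| *2.5% higher* | 95% | 97.5% | 92.5% | 98 / 100 / 95% |
| *Equal* | 96.7% | 96.7% | 91.7% | 97 / 96 / 91% |

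The row sizes are fixed elsewhere. Trial design allocates "1:2:2:2 to the standard licensed 12-week treatment versus 4-week treatment with PEG-IFN + DAA" and the other two strategies, then "1:1 to adjunctive ribavirin versus no ribavirin for the duration of their DAA treatment" among patients not on standard treatment. Sample size gives "156 in the control group and 312 per intervention group for the strategy comparison", "468 per group for the ribavirin comparison" and "546 per group for the regimen comparison".

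Sample size also reports, "assuming that the overall cure rate is 95%, the fixed total sample size of 1092 patients above provides 97% power" for the regimen comparison, and 96% for the strategy comparison. The abstract and the text after Table 5 conclude that power exceeds 90% whatever the control cure rate.

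**The concern.** The table is meant to hold the overall cure rate at 95% and show how power responds to the control and ribavirin assumptions. Standard treatment has one seventh of the patients and each ribavirin half of the shortened groups has three sevenths, so the rows cannot be averaged as equals. If the outer columns miss 95%, they differ from the middle column in overall rate as well as in the assumption being varied. The differences in power between columns then mix two causes, and the printed powers do not answer the question in the table's title.

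**Working it through.** **Inputs.** Group sizes of 156, 468 and 468 (Sample size; they agree with 1:2:2:2 followed by 1:1, that is 1:3:3); 546 per regimen; 14 groups of 78; the Table 5 rates; margins of 5 and 10 points; one-sided alpha 0.05 for non-inferiority and two-sided 0.05 for superiority; logistic regression with marginal effects on 5000 simulated datasets (Statistical analysis).

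**1. Overall rate from the printed figures.** Overall = (156 × standard + 468 × with ribavirin + 468 × without) / 1092.

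- *5% higher*: (156 × 93.3 + 468 × 98.3 + 468 × 93.3) / 1092 = 95.44%
- *2.5% higher*: (156 × 95 + 468 × 97.5 + 468 × 92.5) / 1092 = 95.00%
- *Equal*: (156 × 96.7 + 468 × 96.7 + 468 × 91.7) / 1092 = 94.56%

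If the printed rates are rounded thirds (93.33, 96.67 and so on), the outer columns are 93.33 + (3/7) × 5 = 95.48% and 96.67 − (3/7) × 5 = 94.52%.

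**2. What reproduces 95%.** Equal weights do: (93.33 + 98.33 + 93.33)/3 = 95.00 and (96.67 + 96.67 + 91.67)/3 = 95.00. The middle column gives 95% either way, because its standard rate is the midpoint of the two shortened rates.

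**3. Rates that meet the constraint under 1:3:3.**

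- *5% higher*: x + (3/7) × 5 = 95, so x = 92.86; rates 92.9 / 97.9 / 92.9
- *Equal*: y − (3/7) × 5 = 95, so y = 97.14; rates 97.1 / 97.1 / 92.1

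These differ from the printed rates by about 0.4 to 0.5 points, in a table given to 0.1, so rounding does not explain the gap.

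**4. Do the printed powers go with the printed rates?** Yes. A 5000-dataset simulation used 14 cells of 78, a main-effects logistic model for regimen, strategy and ribavirin without the genotype term, and delta-method risk differences. It reproduces every entry to within 1 point.

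| Column | Printed | Simulated, tabulated rates (unrounded) | Simulated, corrected rates |
|---|---|---|---|
| *5% higher* | 99 / 100 / 98 | 99.0 / 100 / 97.9 | 98.2 / 100 / 96.5 |
| *2.5% higher* | 98 / 100 / 95 | 98.6 / 99.7 / 95.0 | unchanged |
| *Equal* | 97 / 96 / 91 | 97.7 / 96.8 / 91.3 | 98.4 / 98.1 / 93.4 |

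(Regimen / strategy / ribavirin power, %.) Repeat simulations put corrected ribavirin power at 96.4–96.9% and 93.2–93.6%. The Monte Carlo standard error near 93% is √(0.93 × 0.07 / 5000) = 0.4 points.

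**5. Closed-form cross-check.**

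- Regimen: Φ[0.05 / √(2p(1−p)/546) − 1.645]. At p = 0.9548, 0.95 and 0.9452 this gives 99.0%, 98.4% and 97.7% (97.65%). With p = 0.95 throughout it is 98.4% in every column.
- Ribavirin: Φ[(0.05 − 1.96·SE₀)/SE₁], with 468 per arm, SE₀ pooled and SE₁ unpooled. It moves from 97.0% to 95.4% in *5% higher* and from 90.5% to 92.6% in *Equal*: the same directions and similar sizes.

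**6. Effect on the comparison between columns.** In closed form, the whole regimen gradient comes from the unequal overall rates. The simulated ribavirin spread falls from 97.9 − 91.3 = 6.6 points to 96.5 − 93.4 = 3.1 points.

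**The case against.** The strongest reply is that nothing the article concludes depends on this. The shifts are about 0 to 2 points, and every corrected power exceeds 90%. The weakest column, *Equal*, is understated, so the error there is on the cautious side. Only *5% higher* is overstated, where printed power is already 98–100%. All of that stands, and it limits the point to correcting a table.

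The equal-weight explanation is an inference, because the article does not say how the rates were derived. The thirds pattern makes it very likely, but the discrepancy does not depend on the cause.

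Three stronger readings are tempting and not supported:

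- **That the claim of more than 90% ribavirin power fails.** A reader might apply the 5% loss to follow-up from Sample size to the printed *Equal* rates and get 89.4% by normal approximation. Table 5 is stated for 1092 patients with no loss deducted, and the 5% belongs to the single-group calculation of 39 patients. The figure also uses the rates that need correcting; at the corrected rates with the same loss it is 91.5%. Simulations at the printed rates with 74 per group fell on either side of 90% (89.6% and 90.3%).
- **That the 97% and 96% in Sample size come from the *Equal* column.** The numbers match, but that section attributes them only to initial calculations on all 14 groups and does not cite the table.
- **That the abstract must change.** Its statement holds at an actual 95% overall rate.

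**Conclusion.** The statement that each column has a 95% overall cure rate in 1092 patients is wrong for two of the three columns. The actual rates are about 95.5% and 94.5% (95.4% and 94.6% from the rounded entries). This part is plain arithmetic on the article's own group sizes.

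The outer-column powers are therefore attached to the wrong overall rate. The sizes given for a true 95% are simulation results and rest on full group sizes, no stopped groups, no loss to follow-up and a main-effects model without genotype. The error is small and leaves the sample size, margins and stopping guideline untouched. It does distort what the table was built to show: part of the apparent sensitivity to the control and ribavirin assumptions, including essentially all of the regimen trend, is a by-product of unequal overall rates.

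**What to change.** Either of two changes resolves it:

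1. Replace the outer-column rates (control / with ribavirin / without ribavirin) with 92.9 / 97.9 / 92.9 and 97.1 / 97.1 / 92.1, and rerun the power rows with the existing simulation code.
2. Keep the rates and powers, label the outer columns with their actual overall rates, and drop the claim of a common 95% from the title and note.

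The first is better, because it restores the comparison the table intends. In either case, state the 1:3:3 weights in the note. Check whether the 97% and 96% in Sample size were taken from the *Equal* column, and update them if so. No rerun with loss to follow-up is part of this correction.

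The cost is one rerun of an existing simulation, edits to two columns of one table, and possibly one sentence.

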### Limitations of the design

A potential weakness in the design is that the sample size was not originally calculated using Bayesian principles, but primary analyses will be conducted using Bayesian methods to allow for the calculation of posterior probabilities exploring the difference in cure rates between the interventions. However, for the non-inferiority comparisons, sample size estimates obtained using Bayesian methods are similar to or smaller than those obtained using frequentist methods [34], suggesting that our design is likely to be conservative. Additionally, secondary analyses will use frequentist methods for comparison. For interim analyses, the probability of correctly stopping a group, analogous to the frequentist concept of power, is determined by the true cure rate in the group and the number of analysed patients at each analysis and not by the overall group size.

The timing of and the number of patients at interim analyses are determined by at least one group, usually the 4-week treatment group with PEG-IFN since this has the shortest overall treatment duration, reaching a certain probability threshold of being stopped. This may mean delays in identifying unsuccessful groups receiving other strategies. This is unlikely if groups have cure rates lower than the average cure rate because, as discussed above, these will be detected faster than anticipated, but delays may occur if the cure rate is above the average but less than 90%. As the treatment length of patients in the RGT groups is unknown until after their day 7 visit, it is not possible to stagger treatment start dates so that the length between randomisation and EOT is the same for all strategies. Staggered treatment start might also lead to dropout after randomisation but before starting treatment, leading to inefficiency and potential bias. During the trial, cure rates will be monitored in all groups. If the cure rates are not as anticipated, either they are higher and lower than expected, and so our derived schedule is inappropriate based on these cure rates then the timing can be adjusted wih no penalty to the probability of incorrectly stopping recruitment into a randomised group, due to the use of Bayesian monitoring [22].

The power calculations for the final analysis assume that all groups will be included and that no groups have been stopped. It is possible that power will be lower if fewer groups are included, but for most comparisons with a full sample, power is very high and is likely to remain acceptable at the final analysis even with the exclusion of some patients. To help preserve power, if groups are stopped early subsequent patients will be randomly assigned to open groups. The power calculations were also estimated by using frequentist methods, although the primary analysis will use Bayesian methods. However, as power is extremely high, the analogous concept to power in Bayesian analysis, that for non-inferiority comparisons the lower credible interval bound is above the non-inferiority margin, is likely to be similarly high. Additionally, owing to the many possible combinations of strata and groups that could be stopped with different true and observed failure rates and at different times, examining the impact of stopping multiple combinations would require a large number of assumptions, probably also using a factorial simulation design, and hence would be a large piece of additional work in its own right. This is also the case for examining the impact of stopping multiple randomly assigned groups on other aspects of the trial, such as bias.

